## Abstract

**Background:**

International guidelines of groin hernia treatment strongly recommend to fixate the mesh in large M3 medial defects during TAPP/TEP procedures. The main purpose of fixation is to decrease the recurrence rate which is alarmingly high in case of those defects. In 2022, a team consisting of hernia surgeons and scientists from universities of technology conducted an experimental study with the use of 3D groin model to verify the hypothesis that fixation is not necessary in above cases. Experiment showed that rigid and anatomically shaped meshes are able to maintain its position in the groin without fixation. Similar conclusions were recently published in Swedish database registry analysis. To confirm above results, we decided to conduct a multicenter randomized controlled trial.

**Methods:**

Main objective of MEFI Trial is to verify the hypothesis that non-fixation of spatial, standard polypropylene meshes *is non-inferior* to fixation of flat, polypropylene lightweight meshes in M3 hernias by laparoendoscopic approach. Eleven large surgery centers in Poland having proficiency in laparoendoscopic groin hernia repairs were recruited for this study. Recurrence in 12-month follow-up was set as a primary endpoint. Pain sensation (Visual Analog Scale) and incidence of other complications (hematoma, seroma, SSI) were also noted. Based on the statistical analysis, minimal sample size in both arms was established at 83–102. The first arm (control) consists of patients undergoing a repair with the use of a flat, macroporous mesh with fixation using histoacryl glue. In the second arm, patients will be operated with the use of anatomically shaped, standard-weight mesh without fixation. Study will be double-blinded (patient/surgeon). After the dissection of preperitoneal space, surgeon will open a sealed envelope and find out which technique he will have to perform. Follow-up will be performed by Study Secretary (also blinded to the method used) via phone call 3 and 12 months after surgery.

**Discussion:**

Based on experimental study and recent registry analysis, we believe that the recurrence rate in both groups would be on the same level, giving hernia societies a strong argument for amending the guidelines.

**Trial registration:**

ClinicalTrials.gov NCT05678465. Registered on 10 January 2023.

## Administrative information

Note: the numbers in curly brackets in this protocol refer to SPIRIT checklist item numbers. The order of the items has been modified to group similar items (see http://www.equator-network.org/reporting-guidelines/spirit-2013-statement-defining-standard-protocol-items-for-clinical-trials/).

## Introduction

### Background and rationale {6a}

Every year, more than 20 million people worldwide are operated on for inguinal hernias. The methods of choice are laparoendoscopic techniques if the appropriate equipment and trained personnel are available [1]. TAPP and TEP are gradually replacing classical methods (including the Lichtenstein method) as first-line treatment. Although in laparoendoscopic methods, mesh fixation is not recommended, with the exception of large direct hernias (M3). The 2018 international guidelines contain a strong recommendation for mesh fixation for M3 defects [1].

The basis for formulating this recommendation is the analysis of the German Hernia Registry (HerniaMed) published by Meyer et al. in 2017 on 11,230 cases [2]. During the multivariate analysis, it was noted that the recurrence rate in the case of large M3 inguinal hernias was alarmingly high, and the implant fixation significantly reduced the recurrence rate in those cases. Despite weak scientific evidence, the recommendation was upgraded to strong status by a panel of experts.

In 2022, a multidisciplinary team consisting of surgeons and scientists from the Warsaw and Cracow Universities of Technology conducted a research experiment aimed at checking the behavior of implants in the operating field under the highest possible intraabdominal pressure. Based on the previously constructed groin model, tests of implants used during laparoendoscopic repairs of inguinal hernias were carried out. Results confirm the hypothesis that in the case of large M3 hernias, the key role in maintaining the implant in the operating field is the type of mesh (stiffness, appropriate margin, spatial shape) rather than its fixation. Only stiffer, anatomically matched implants were able to maintain mechanical stability under pressure surges. Flat, macropore implants in the vast majority of the Herniamed registry were “shot” through the hernial orifices and lost their initial position, thus giving room for rapid recurrence [3].

In the same year, Novik et al. published data from the Swedish Hernia Registry, where, similarly to the work of Meyer et al., they analyzed the results of patients treated for inguinal hernias in 2005–2017 [4]. 25,190 patients were analyzed and a multifactorial analysis was used to correlate the type of implant used, the size of the hernia, and the risk of recurrence. Conclusions coincide with those presented by Zamkowski et al.

In order to confirm experimental results and conclusions contained in the analysis of Swedish hernia registries, a decision was made to conduct a multicenter, randomized, double-blind clinical trial. The aim will be to prove that the lack of fixation of a standard, anatomic spatial mesh is noninferior to the fixation of a light, macroporous flat mesh in the case of large M3 hernias operated laparoendoscopically.

Confirmation of the conclusions from experimental work and retrospective analysis of the Swedish hernia registry through a randomized controlled trial will give rise to a change or update of international guidelines for the treatment of inguinal hernias.

### Objectives {7}

Main objective of MEFI Trial is to verify the hypothesis that non-fixation of spatial, standard polypropylene meshes *is non-inferior* to fixation of flat, polypropylene lightweight meshes in M3 hernias by laparoendoscopic approach in terms of recurrence.

### Trial design {8}

MEFI Trial is a prospective, non-inferiority, parallel, two-armed, multicenter, double-blinded randomized controlled trial to study outcomes of non-fixation of the mesh in terms of recurrence in large M3 defects during laparoendoscopic hernia repair techniques. Eleven large surgery centers in Poland, proficient in laparoendoscopic groin hernia repairs (performing at least 80 TAPP/TEP procedures a year), were selected for this study (Table 1 and Fig. 1). List of study sites (collaborators) is given in the Organizational Structure and Responsibilities section at the end of document. Recurrence rate in 12-month follow-up was set as a primary outcome.

**Table 1 Tab1:** Schedule of enrolment, interventions, and assessments for the MEFI trial

	**Study period**					
	**Enrolment**	**Allocation**	**Post-allocation**			**Close-out (unblinding)**
**Timepoint**	*** − (1–2) weeks***	**0**	***7–10 days***	***3 months***	***12 months***	***12 months***
**Enrolment:**						
**Eligibility screen**	X					
**Informed consent**	X					
***Surgery (TAPP/TEP)***		X				
**Allocation**		X				
**Interventions:**						
***FIXATION of flat macroporous lightweight mesh—CONTROL***		X				
***NON-FIXATION of 3D, anatomical StdPPM***^a^		X				
**Assessments:**						
***Recurrence rate—primary endpoint***			X	X	X	X
***Pain sensation—secondary outcomes***			X	X	X	X
***Other complications***^b^***—other outcomes***			X	X	X	X

^a^Standard pure polypropylene mesh

^b^Other complications: hematoma, seroma, and surgical site infection

**Fig. 1 Fig1:**
[figure not shown]
Flow-diagram of MEFI Trial

## Methods: participants, interventions, and outcomes

### Study setting {9}

Eleven large surgery centers in Poland, proficient in laparoendoscopic groin hernia repairs (performing at least 80 TAPP/TEP procedures a year), were selected for this study (Table 1 and Fig. 1). List of study sites (collaborators) is given in the Organizational Structure and Responsibilities section at the end of document. Recurrence rate in 12-month follow-up was set as a primary outcome. Swissmed Hospital in Gdańsk, Poland, is responsible for the coordination of MEFI Trial, as well as, for conducting the phone call follow-up protocol. Also, it is the central point of contact for study participants and surgeons. Study participants will be recruited in collaborating hospitals and in coordinating unit. Study Secretary and Study Chief will be known to participants and they will be given their e-mail and phone number to stay in constant contact. Study Chief and Study Director along with Study Secretary and two volunteers from collaborators centers will be form the Trial Steering Committee. The Trial Steering Committee will meet once a month to exchange information and evaluate recent data. Study group will also have access to WhatsApp group and Facebook closed group to exchange comments/observations and provide organizational support. Study Chief, Study Director, and Study Secretary will be available to all study participants and other collaborators 24/7. Data will be managed by each surgeon designated from collaborators centers. All designated surgeons will form the Data Management Team.

### Eligibility criteria {10}

Patients undergoing elective groin hernia repair will be initially recruited for the study. Inclusion and exclusion criteria are listed in Table 2. As M3 Hernias are difficult to diagnose before the surgery, all patients scheduled for laparoendoscopic repairs will be asked to participate. Final recruitment to the study will take place after placing visual track and measuring the size of defect. Informed verbal and written consent will be obtained by the surgeon performing the operation. GDPR (General Data Protection Regulation) consent will be taken by the medical secretary on admission to the hospital.

**Table 2 Tab2:** Inclusion and exclusion criteria in the MEFI trial

Inclusion criteria	Exclusion criteria
Elective groin hernia repair	Age < 18 years
Age > 18 years	Eemergency surgery (incarcerated hernia)
Male and female patients can participate	Contaminated surgical field
M3 or M3 + L1-3 (EHS classification) groin hernia confirmed during surgery	Recurrent hernia
Eligibility for laparoendoscopic repair	Extremely large scrotal hernias with the need of other abdominal compartment syndrome (ACS) preventive procedures (botulin injection, bowel resection, preoperative progressive pneumoperitoneum (PPP))
Signed written informed consent	

### Who will take informed consent? {26a}

Informed verbal and written consent will be obtained by the surgeon performing the operation.

### Additional consent provisions for collection and use of participant data and biological specimens {26b}

On the consent form, participants will be asked if they agree to use their data should they choose to withdraw from the trial. Participants will also be asked for permission for the research team to share relevant data with people from the Universities taking part in the research or from regulatory authorities, where relevant. This trial does not involve collecting biological specimens for storage.

## Interventions

### Explanation for the choice of comparators {6b}

First arm, also serving as control group, will consist of patients operated with the use of flat, macroporous, lightweight mesh fixated with the use of histoacryl glue. This method is currently recommended for large M3 hernias in 2018 European Hernia Society Guidelines. Second arm (experimental group) will consist of patients operated with the use of anatomically shaped, large, standard polypropylene mesh (Dextile Anatomical Mesh – MEDTRONIC™ (Dublin, Ireland) or 3D Max Mesh – BD™ (New Jersey, USA)) without the use of fixation material. The effectiveness of method is supported by recent publications published in 2022 by Zamkowski et al. and Novik et al. [2, 3].

### Intervention description {11a}

As M3 hernias are difficult to diagnose before the surgery, all patients scheduled for laparoendoscopic repairs will be asked to participate. After the dissection, reduction of hernia sack, and creation of preperitoneal space, the surgeon will open a sealed envelope and find out what technique he/she will have to perform and participants will be randomly allocated to one arm of the study. Dissection of preperitoneal space and placing the mesh in the groin area are considered to be the most important stage of the procedure—every surgeon will have to take visual record of that part of surgery to make sure proper technique was applied. Patients will not be aware of the method used during surgery. When using fixation material with histoacryl glue, it will be placed in previously predefined places (Fig. 2). Before recruiting patients, a 2-day “bootcamp” meeting was scheduled. Each center designated one surgeon responsible for conducting the trial in their hospital and sent him/her to attend the meeting. The meeting consisted of lectures on the first day and exhibition surgeries performed by experts on the second day. A meeting took place to unify the surgery technique and make sure every center will follow the same protocol. After operation, surgeon will fill the study form and put it in a sealed envelope. All patients in both arms will be given standard recommendation to avoid intensive physical activity for 2 weeks post-op. Standard wound care will be explained to patients in both groups.

**Fig. 2 Fig2:**
[figure not shown]
Landmarks to place histoacryl glue during mesh fixation

### Criteria for discontinuing or modifying allocated interventions {11b}

Participants of the study can withdraw their consent to take part at any time. The principal investigator may exclude patients from the study, if patients’ safety is at risk. In order to generate a meaningful database, excluded patients can be replaced by the recruitment of new patients.

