#### Primary outcome

The primary endpoint is the recurrence rate in 1-year follow-up.

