### Participant timeline {13}

All patients undergoing elective inguinal hernia repair, meeting the inclusion criteria for the study, will be asked to participate and given informed written consent. After creating a pneumoperitoneum and placing a vision trocar, the hernia defect will be measured. If the presence of a simple M3 hernia (or a complex M3 hernia with a component of an oblique hernia) is confirmed, full inclusion in the study will take place. After the next stages of the operation, i.e., placement of working trocars, release of adhesions, and dissection of the preperitoneal space with reduction of the hernial sac, the stage of random allocation to the study arms will take place by opening the envelope and learning the technique to be used in a given participant. After the procedure, the surgeon will fill out the researcher’s card and place the operating protocol in a prepared coded envelope. The participant will receive information about full inclusion in the study and full follow-up. A follow-up visit 7–10 days after the surgery will take place in the hospital outpatient clinic, during which further information about the health condition will be collected, and a physical examination will be performed. Both groups will receive the same standard postoperative recommendations. Subsequent follow-ups (3 months and 12 months after) will take place through a telephone conversation made by study secretary blinded to the method used. Detailed timeline is presented in Table 1.

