## Assignment of interventions: allocation

### Sequence generation {16a}

Randomization will be performed with the use of the Clinical Trial Randomization Tool (National Cancer Institute) on 1:1 basis by Study Secretary. Based on randomization, 204 envelopes will be prepared, each with a unique code number. Inside, apart from blank research cards to be completed, there will also be a smaller envelope with the type of technique to be used during the procedure. Participants, the Study Secretary, and surgeons will be blinded in terms of allocation to individual arms (until the envelope is opened). Unblinding will take place at the end of the trial via phone call (or ambulatory visit if one will be scheduled) by Study Secretary.

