The trial was planned as non-inferiority study with test power = 80%, *p*-value = 0.05, and threshold for clinical significance = 8%. A percentage loss of 10% was assumed. Recurrence rate was assumed to be 4% based on literature data. Based on those assumptions, minimal sample size in both arms was established at 83–102. To ensure sufficient participant numbers at completion of the trial, sample size was established at 204 participants. To maintain the integrity and clarity of our results, we chose to focus on our primary analysis. Given the focused nature of our primary research question and to maintain the power of our statistical analyses, we opted not to divide our sample further into subgroups.

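### Safety exclusions may be refilled with new recruits, and the rule is not limited to the time before the envelope is opened, so it can bias the non-inferiority comparison

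*Protocol article*

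**What the plan says.** Under Criteria for discontinuing or modifying allocated interventions {11b}, the protocol article states: "The principal investigator may exclude patients from the study, if patients’ safety is at risk". The next sentence is the replacement rule: "In order to generate a meaningful database, excluded patients can be replaced by the recruitment of new patients". Exclusion is from the study, not from the allocated technique, and no time limit is attached to either step.

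Participant timeline {13} gives the order of events: consent, measurement of the defect, full inclusion if an M3 hernia is confirmed, dissection, and then "the stage of random allocation to the study arms will take place by opening the envelope". Mesh placement follows. Who will be blinded {17a} names the participants and the Study Secretary, and the surgeon only up to that moment. The principal investigator is not named there.

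The design is given as follows: "MEFI Trial is a prospective, non-inferiority, parallel, two-armed, multicenter, double-blinded randomized controlled trial". On the outcome: "The primary endpoint is the recurrence rate in 1-year follow-up". The article's section on non-adherence and missing data {20c} describes video review of technique and does not mention excluded patients.

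**The concern.** Randomisation protects the comparison only for the patients who stay in it. Once the envelope is open, the surgeon knows the arm, and a safety problem that then leads to exclusion may be related to the mesh, to its fixation or to an impending recurrence. If such a patient leaves the study and a new recruit fills the place, a possible failure is exchanged for a patient with an ordinary risk.

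In a superiority trial this mostly blurs a difference. In a non-inferiority trial, blurring a difference favours the claim. The trial is also sensitive to single patients: at the planned 4% recurrence, 92 evaluable patients give 0.04 × 92 = 3.7 expected recurrences per arm.

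An analysis plan cannot fully repair this afterwards. It can define who is analysed, but a patient excluded from the study may have no 12-month recurrence result to analyse.

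**Working it through.** **Inputs.** From Sample size {14}: recurrence 4%, margin 8 percentage points (read as an absolute difference), power 80%, level 0.05 with sidedness not stated, loss 10%. From {20a}: 204 in total, so 102 per arm and 102 × 0.9 = 91.8, about 92 evaluable. The share f of would-be failures that are excluded and replaced is an assumption.

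**The plan's own figure.** n per arm = 2 × 0.04 × 0.96 × (z₁₋α + z₀.₈₀)² / 0.08².
- One-sided 0.05: 74.2; divided by 0.9 this is 82.4, so 83. It matches the lower stated figure.
- One-sided 0.025: 94.2; divided by 0.9 this is 104.7, so 105. It is close to the upper figure of 102 but not equal to it.

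Both levels are therefore carried forward.

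**Step 1: how few patients matter.** The Newcombe upper limit is d + √[(u_T − p_T)² + (p_C − l_C)²], with Wilson limits u and l for each arm.
- 6/92 without fixation v 4/92 with fixation, two-sided 95%: d = 0.0217, u_T = 0.1351, l_C = 0.0170. The limit is 0.0217 + √(0.0698² + 0.0264²) = 0.096, or 9.6 points, above the margin of 8.
- If two of the six failures are excluded and replaced by two patients without recurrence, 4/92 v 4/92: d = 0, u_T = 0.1065. The limit is √(0.0630² + 0.0264²) = 0.068, or 6.8 points, below the margin.

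Two patients reverse the conclusion in this example. At one-sided 5% the first limit is 8.3 points, only just above the margin, so there the example is a near miss that turns into a pass.

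**Step 2: effect on the error rate.** Suppose the truth lies at the margin: 12% without fixation, 4% with it. If a share f of failures is excluded and replaced, the analysed rate becomes p(1 − f)/(1 − pf). For p = 12% this gives 11.5%, 10.9%, 9.8% and 8.3% at f = 5%, 10%, 20% and 33%. For p = 4% it gives 3.8%, 3.6%, 3.2% and 2.7%. The false non-inferiority rate is the exact binomial probability, summed over all pairs of counts with 92 per arm, that the Newcombe upper limit lies below 8 points.

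| Failures removed | Non-fixation arm only, one-sided 2.5% | Both arms, one-sided 2.5% | Non-fixation arm only, one-sided 5% | Both arms, one-sided 5% |
|---|---|---|---|---|
| none | 2.3% | 2.3% | 4.8% | 4.8% |
| 5% | 3.1% | 2.7% | 6.3% | 5.7% |
| 10% | 4.1% | 3.3% | 8.1% | 6.8% |
| 20% | 7.2% | 4.9% | 13.4% | 9.8% |
| 33% | 14.8% | 8.3% | 24.8% | 15.8% |

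For scale, 12% of 92 is about 11 failures, so 10% removed is about one patient and 33% is between three and four.

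Removing equal shares from both arms still inflates the error, because it shrinks the absolute difference: at f = 20%, from 8.0 points to 9.8 − 3.2 = 6.6. Removing failures from the fixation arm alone widens the difference and works against non-inferiority.

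**The case against.** Several stronger readings are tempting, and the documents do not support them.

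- **That exclusion is at the investigator's free discretion.** It is tied to patient safety. That narrows the rule, although safety problems after surgery are the ones most likely to be related to treatment or outcome.
- **That every such exclusion comes after randomisation.** It need not. Full inclusion follows measurement of the defect, and the envelope is opened only after dissection, so a patient can be excluded between the two. Replacing that patient does no harm. The section heading is a reporting-checklist label and is weak evidence of timing. The defect is that the sentence does not separate the two periods.
- **That the rule does remove recurrences and does tilt the result.** Recurrence is nowhere named as a ground for exclusion. The intervention is given once, so exclusions after surgery may be few. The documents support only that the rule can have this effect.
- **That excluded patients' data are discarded.** The article does not say so, and an analysis plan that is not shown may define the analysis sets. Equally, nothing in the article keeps these patients in follow-up.
- **That replacement counts the 10% allowance twice.** Of the allowance the article says: "A percentage loss of 10% was assumed". Elsewhere ({15} and {18b}) it ties 10% to loss to follow-up, which is a different category from safety exclusion.
- **That the randomisation list contradicts the rule.** Sequence generation {16a} says "204 envelopes will be prepared, each with a unique code number", and no spares are mentioned. A condensed article may leave such logistics to the full protocol.

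What remains is a rule, stated in the text, that permits replacement after allocation.

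**Conclusion.** The point holds as a defect in a stated rule: study exclusion on safety grounds with replacement, and no boundary at the opening of the envelope. Applied after allocation, it can remove recurrences and bias the comparison, usually toward non-inferiority.

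The size is unknown because no exclusion rate is given. Under the assumptions above, it runs from slight (2.3% to 2.7%, or 4.8% to 5.7%, when 5% of failures are removed from both arms) to serious (14.8% or 24.8% when a third are removed from the non-fixation arm alone). The upper end is a deliberately high assumption and not a forecast. The results also assume an absolute 8-point margin, true rates at that margin, 92 evaluable per arm and replacements drawn at the arm's ordinary risk. The correction is worth making because the rule bears on the only primary claim and costs almost nothing to repair.

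**What to change.** Replace the sentence on replacement in {11b} with text to this effect: a patient excluded before the envelope is opened is not randomised and may be replaced. Once the envelope is opened, the patient is not replaced, is followed to 12 months whatever technique was used (unless consent for follow-up is withdrawn), and is analysed in the allocated arm.

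This leaves clinical freedom to depart from the technique as it is; it bars only removal from follow-up and from the comparison. The planned 204 does not change. At about 92 evaluable per arm, the same normal approximation as in the plan's sample size gives power of 87% at one-sided 5% and 79% at one-sided 2.5%. The cost is a wording amendment, and a few off-protocol patients will stay in the denominator.
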